### Statistical plan

#### Sample size

The primary objective for the phase II is the feasibility of the study. The SPEP participation will be considered sufficient if a patient has performed at least 50% of the theoretically planned sessions within 3 months (supervised and non-supervised). With a unilateral alpha risk of 5%, a statistical power of 85%, a probability of inefficiency maximum of 50%, a probability of minimum efficiency of 65%, and a 5% lost to follow-up rate, 120 patients will need to be randomized in the phase II with a 2:1 ratio (74 patients in the SPEP; 37 patients in the control arm of recommended adapted physical activity). Patients will be included in a non-competitive manner in the different cohorts. An interim analysis is planned when 37 patients will be randomized in the SPEP arm with rejection of H0 if at least 27 patients have completed at least 50% of the planned sessions; rejection of H1 (futility) if 19 patients or less have completed at least 50% of the planned sessions.

The phase III study will evaluate the 3-month efficacy of the SPEP, compared to recommended adapted physical activity. The 120 patients randomized in the phase II will be included in the phase III analysis. The co-primary endpoint criteria are the fatigue score (using FACT-F) and the physical well-being score (using FACT-G) evaluated after 3 months. SPEP superiority over the recommended adapted physical activity program will be demonstrated if at least one of the criteria (FACT-F or FACT-G) increase significantly without deterioration of other criteria. To demonstrate a clinically significant difference of at least 5 points (standard deviation: 13) for the physical well-being dimension of the FACT-G questionnaire and at least 2.5 points (standard deviation: 6.5) for FACT-F questionnaire at 3 months [17, 18], with a bilateral alpha risk of 2.5%, a statistical power of 80%, and a 5% lost to follow-up rate, 312 patients will need to be randomized in the phase III. The inclusions will be non-competitive between the 4 cohorts (78 patients per cohort). A 30-month inclusion period is predicted for the recruitment of these 312 patients in 18 French centers. An interim analysis is planned at the end of the phase III corresponding to 39.5% of patients randomized in order to reject H0 or H1 according to alpha spending function.

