### Statistical analysis

For the phase II, all the analyses will be non-comparative and performed on the intention-to-treat (ITT) population: all patients included in the study irrespective of the respect of the study.

For the phase III, analyses will be performed on the modified ITT (mITT) population: ITT patients with FACT-F and physical well-being score available at baseline and M3. Longitudinal analysis of QoL data will be performed on a mITT2 population: ITT patients with FACT-F and physical well-being score available at baseline. Quantitative analyses will be described by the mean (standard deviation) and median (minimum-maximum) values while qualitative and categorical analyses will be reported by frequency and percentage. A description of FACT-F, FACT-G, and FACT-Cog scores will be done by arm for each time point with the mean (standard deviation) and median (minimum-maximum) values. The statistical analysis will be performed using t-test, log-rank, stratified log-rank, invariable analysis, and multivariable analysis.

For the co-primary endpoint, a t-test will be done to compare FACT-F and physical well-being scores at 3 months according to the study arms, at the statistical level of 2.5%, after checking the normality of the scores and potential transformation of the scores. An analysis of variance for repeated measure will also be done taking into account the baseline score. Then, some univariate and multivariate models will be done in order to identify factors associated with the change of fatigue and physical well-being score between baseline and 3 months. All factors with an univariate *p*-value < 0.1 will be eligible for the multivariate models.

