### Randomization

Randomization, achieved using the Clinsight® software, will take place within 15 days of the initiation of the targeted therapy. Patients will be allocated to either the experimental SPEP group or the recommended adapted physical activity group in a ratio 2:1. Randomization will be stratified per site, baseline level of fatigue, targeted therapy, number of lines of prior therapy in the metastatic status, and age.

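### The deciding phase III test is an unadjusted t-test of month-3 scores with an optional transformation, although every analysed patient has a baseline score and randomisation is stratified on baseline fatigue

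*Protocol article*

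**What the plan says.** The Statistical analysis section fixes the co-primary analysis: "a t-test will be done to compare FACT-F and physical well-being scores at 3 months according to the study arms", at the 2.5% level, "after checking the normality of the scores and potential transformation of the scores". It then adds: "An analysis of variance for repeated measure will also be done taking into account the baseline score". That second analysis has no significance level, no stated month-3 contrast and no link to the superiority rule. Univariate and multivariate models of change follow, with factors screened at p < 0.1.

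The phase III modified intention-to-treat population consists of patients with both scores at baseline and at month 3.

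Under Randomization: "Randomization will be stratified per site, baseline level of fatigue, targeted therapy, number of lines of prior therapy in the metastatic status, and age". Allocation is 2:1.

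Sample size assumes "at least 5 points (standard deviation: 13) for the physical well-being dimension of the FACT-G questionnaire". For fatigue it takes a FACT-F difference of 2.5 with an SD of 6.5. The other terms are a two-sided alpha of 2.5%, 80% power, and "a 5% lost to follow-up rate, 312 patients will need to be randomized in the phase III".

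**The concern.** Three features of the deciding test look badly chosen.

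- **No baseline term.** A patient's own baseline score is usually among the best predictors of the same score three months later. Leaving it out keeps explainable variation in the error term and leaves any chance baseline difference in the estimate. Baseline fatigue is at least a stratification factor; baseline physical well-being is not, so nothing in the design or the test controls it.
- **Strata ignored.** Stratifying on a prognostic factor makes the difference between arms less variable than under simple randomisation. An unadjusted t-test computes its standard error as if that had not been done, so the standard error is too large.
- **Scale left open.** The primary result may be moved to a transformed scale after the outcome data have been examined, with no trigger or transformation named. Clinical significance is defined in points (2.5 for FACT-F, 5 for physical well-being), and a difference on a transformed scale cannot be read against those thresholds.

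At stake are power and precision on both co-primary endpoints, and a primary result that depends on a look at the data. Inflation of the type I error by the unadjusted test is not at stake.

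**Working it through.** **Inputs from the protocol article.** Differences and SDs 5/13 and 2.5/6.5, both giving d = 0.385; two-sided alpha 2.5%; power 80%; 5% loss; 312 randomised (Sample size). Allocation 2:1 (Randomization).

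**Assumed.** The baseline to month-3 correlation r, which the document does not give; and that 13 and 6.5 are SDs of month-3 scores, not of changes.

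**1. The plan's own figure.** For 2:1 allocation the control arm needs

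n = (1 + 1/2) × (z₀.₉₈₇₅ + z₀.₈₀)² × (SD/difference)² = 1.5 × (2.241 + 0.842)² × (13/5)² ≈ 96.4, so 97.

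The total is 97 + 194 = 291, and 291/0.95 = 307. The exact noncentral t needs 98 + 196 = 294, and 294/0.95 = 310. The stated 312 (four cohorts of 78) is therefore reproduced as an unadjusted two-sample comparison.

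**2. Power of the planned test.** 312 × 0.95 = 296 evaluable, about 197 and 99. The exact noncentral t gives 80.7% (81.0% by normal approximation).

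**3. Power after baseline adjustment.** Residual SD = SD × √(1 − r²), so the effective standardised difference is 0.385/√(1 − r²). The unadjusted t-test would need 296/(1 − r²) evaluable patients to match.

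| r | Variance removed (r²) | Power, 197 v 99 | Matching N, t-test |
|---|---|---|---|
| 0 | 0% | 80.7% | 296 |
| 0.1 | 1% | 81.1% | 299 |
| 0.2 | 4% | 82.4% | 308 |
| 0.3 | 9% | 84.6% | 325 |
| 0.5 | 25% | 91.1% | 395 |
| 0.6 | 36% | 95.0% | 463 |

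Both endpoints have the same d, so the table applies to each.

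**4. Effect of stratified randomisation on the t-test.** Simulation with N = 297, 2:1, blocks of 3, nominal two-sided 2.5%:

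- *Strata formed only by baseline score split at the median.* The t-test's true type I error was about 2.2%, 1.5% and 0.6% at r = 0.3, 0.5 and 0.7 (8,000 runs each). Repeat simulations gave 1.2% to 1.5% at r = 0.5 and 0.4% to 0.8% at r = 0.7. Baseline-adjusted analysis (ANCOVA) stayed at 2.3% to 2.6%.
- *Strata formed by 18 sites and four binary factors* (the number of levels is an assumption). The t-test's type I error was about 2.6%, 1.9% and 1.7% (6,000 runs each, Monte Carlo error about 0.2 points).
- *Power with baseline strata only* (4,000 runs each). t-test against ANCOVA: 82.6% v 85.0% at r = 0.3, 83.9% v 92.1% at r = 0.5, 85.2% v 98.4% at r = 0.7. Stratification recovers a little of the lost power for the t-test, but most of the gap remains at r = 0.5 and above.

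**5. Cost of adjustment in patients.** None, because membership of the phase III population already requires the baseline score.

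**The case against.** The strongest reply is that nothing here is an error. The t-test is valid under randomisation, agrees with the sample size, and reaches its 80% target. That stands, and it limits the severity.

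The size of the gain rests on a correlation the document does not give. Baseline falls around the start of oral targeted therapy, and fatigue is described as an early side effect, so month-3 fatigue may partly reflect toxicity that arises after baseline. At r = 0.1 or 0.2 the gain is under 2 points of power. That stands for the size, not the direction: the gain is positive at every value examined.

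The standard-error argument weakens when all five stratification factors are crossed, because strata then hold very few patients. That stands in part. The distortion disappears within simulation error at r = 0.3, but remains at 0.5 and 0.7.

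Baseline adjustment is already planned through the repeated-measures analysis, and model detail belongs in a statistical analysis plan that is not shown. This does not answer the point. The article itself assigns the 2.5% level to the t-test, and the adjusted analysis decides nothing. Likewise, the details of a transformation can be left to that plan, but the article already makes the primary scale conditional on the outcome data. Reporting raw means and SDs alongside would help interpretation without restoring a primary estimate in points.

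**Conclusion.** The concern holds. The deciding test omits a covariate available for every analysed patient and ignores stratification on that covariate. With 296 evaluable patients, adjustment would lift power from 80.7% to between 84.6% and 95.0% for correlations of 0.3 to 0.6. At r = 0.5 that is worth about 395 evaluable patients analysed by t-test. These figures assume that the stated SDs describe month-3 scores; below r = 0.3 the gain is small. Where the strata carry prognostic information, the t-test's standard error is too large and the test conservative, by an amount that shrinks as strata become sparse.

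The transformation step is a separate weakness. With about 100 and 200 patients per arm, a linear model on raw scores does not need it, and it would detach the result from the 2.5-point and 5-point thresholds.

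This should be changed, but it does not threaten the trial's validity: type I error is not inflated by the unadjusted test and the trial is not underpowered for its own plan.

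**What to change.** For each co-primary endpoint, make the deciding analysis a linear model of the month-3 score on arm, that endpoint's baseline score and the patient-level stratification factors (baseline fatigue level, targeted therapy, prior lines, age), with site as a random effect or pooled if sparse. The month-3 contrast of a repeated-measures mixed model with the same terms would serve equally. Test at two-sided 2.5% and report the difference in points with a 97.5% confidence interval. Use the same model at the phase III interim analysis.

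Delete the normality check and transformation. Keep the raw t-test as a supportive analysis. State that the superiority rule is judged on the adjusted model alone.

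The cost is wording only: no new data and no change to the 312. Because the t-test is named in the published protocol and recruitment was under way, the change may need a protocol amendment as well as text in the analysis plan. It should be fixed before any comparison of outcomes by arm.

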## Aim and research questions

The phase II is a randomized non-comparative study to evaluate the feasibility of a home-based, adapted, standardized, and supervised physical exercise program for patients receiving OTT for a metastatic solid tumor (spared in 4 cohorts: breast cancer, kidney cancer, lung cancer, and other cancers [including but not limited to colon cancer, melanoma, sarcoma, or hepatocarcinoma]). The comparative phase III study aims to evaluate the benefit of a SPEP compared to a recommended adapted physical activity, on fatigue and physical dimension of quality of life of such patients at 3 months.

In both phase II and III, the secondary objectives will include the evaluation of the impact of the SPEP on overall and progression-free survival, general quality of life over time, fatigue over time, pain, psychosocial and cognitive functions, muscle mass, muscle density, adipose tissue (visceral and subcutaneous), weight gain, and body mass index. The physical benefit, patients’ observance and tolerance, and the predictive value of the SPEP on survival, general quality of life, and fatigue will also be evaluated. Investigations will also address the toxicity, frequency of dose reduction, and patients’ adherence to the targeted therapy. Finally, this study aims to explore the correlation between fatigue and muscle mass, and between fatigue and muscle density.

The QUALIOR study also encompasses an ancillary evaluation of the medico-economic impact of the SPEP.

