##### ***Efficacy****,* phase III comparative study

The co-primary endpoint is the fatigue score (using FACT-F questionnaire) and the physical well-being score (using FACT-G questionnaire) evaluated after 3 months. A difference of at least 2.5 points for FACT-F and at least 5 points for the physical well-being score of FACT-G will be considered clinically significant. SPEP superiority over the recommended adapted physical activity program will be demonstrated if at least one of the targeted dimensions (FACT-F or the physical well-being of the FACT-G) is significantly improved without deterioration of the other dimension.

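### Minor efficiency point: both co-primary scores are tested at a fixed two-sided 2.5%, where a Holm step-down would keep the same family-wise ceiling and raise the chance of confirming both

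*Protocol article*

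**What the plan says.** Four places in the protocol article bear on this.

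- **Statistical analysis:** the co-primary t-test is to "compare FACT-F and physical well-being scores at 3 months according to the study arms, at the statistical level of 2.5" per cent. The same level applies to both scores.
- **Sample size:** the phase III number is derived "with a bilateral alpha risk of 2.5%, a statistical power of 80%, and a 5% lost to follow-up rate". The assumed differences are 5 points (SD 13) for FACT-G physical well-being and 2.5 points (SD 6.5) for FACT-F.
- **Efficacy, phase III comparative study:** success requires that "at least one of the targeted dimensions (FACT-F or the physical well-being of the FACT-G) is significantly improved without deterioration of the other dimension".
- **Aim and research questions:** phase III is to evaluate "the benefit of a SPEP compared to a recommended adapted physical activity, on fatigue and physical dimension of quality of life".

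The level, the sizing and the success rule agree with each other: either endpoint suffices, and each gets half of 5%. The 5% total is implied by 2 × 2.5% and is not written out. Nothing in the article lets the second endpoint be tested at a higher level once the first has been rejected.

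**The concern.** With two endpoints and an either-endpoint rule, testing each at 2.5% protects the family-wise error at 5%. Holm's procedure gives the same protection under any correlation. It rejects whenever Bonferroni rejects, and it also tests the remaining endpoint at 5% once the smaller p-value is below 2.5%. A fixed 2.5% on the second endpoint is therefore stricter than family-wise control requires.

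What is at stake is the second claim. Suppose p = 0.01 on one score and p = 0.04 on the other. As written, the trial is positive (if the other score has not deteriorated) but must report the second dimension as not shown. Under Holm both would be confirmed. Since the aim names both fatigue and the physical dimension, the trial's report would differ.

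**Working it through.** **Inputs, all from the article.** Standardised effect 5/13 = 2.5/6.5 = 0.385 on both endpoints; two-sided 2.5% each; 80% power; 5% loss to follow-up; 312 randomised (Sample size); 2:1 allocation (Randomization). The correlation between the endpoints is not given, so 0.3 to 0.8 is assumed. The phase III interim is left out because its spending function is not named.

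**1. The plan's own number.** Control arm n = (1 + 1/2) × (z₀.₉₈₇₅ + z₀.₈₀)² × (SD/difference)² = 1.5 × (2.241 + 0.842)² × (6.5/2.5)² = 96.4, so 97. The SPEP arm needs 194, total 291. Dividing by 0.95 gives 307, against 312 stated (1.6% apart). Neither 1:1 allocation at 2.5% (272) nor 2:1 at two-sided 5% (253) comes close. The sizing is therefore two-sided 2.5% per endpoint with 2:1 allocation.

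**2. Power per endpoint.** Evaluable: 312 × 0.95 = 296.4, or 98.8 and 197.6 per arm. Expected test statistic = 0.385 / √(1/98.8 + 1/197.6) = 3.12. Power at 2.5% is Φ(3.12 − 2.241) = 81.1%; at 5% it is Φ(3.12 − 1.960) = 87.7%.

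**3. Power for both and for at least one.** The two test statistics are taken as bivariate normal, each with mean 3.12. Fixed 2.5%: P(both exceed 2.241). Holm: P(both exceed 1.960 and at least one exceeds 2.241).

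| Assumed correlation | Both, fixed 2.5% | Both, Holm | Gain | At least one (either method) |
|---|---|---|---|---|
| 0.3 | 0.6817 | 0.7787 | 0.097 | 0.9394 |
| 0.5 | 0.7018 | 0.7907 | 0.089 | 0.9194 |
| 0.7 | 0.7265 | 0.8057 | 0.079 | 0.8947 |
| 0.8 | 0.7420 | 0.8148 | 0.073 | 0.8792 |

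Outside that range, the gain is 10.8 points at correlation 0 and 6.3 points at 0.9.

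**4. Chance of confirming a given endpoint.** The gain in step 3 is split equally between the endpoints, so this chance is 81.1% plus half the gain: 81.1 + 4.85 = 85.9% at correlation 0.3, and 81.1 + 3.6 = 84.7% at 0.8. If the second endpoint has only 70% of the planned effect, the chance of confirming it goes from 48% to 57–58%.

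**5. Error rates.** With both endpoints null, the family-wise error is the same under both methods: about 4.9% at correlation 0.3 and 4.0% at 0.8. With the planned effect on one endpoint and none on the other, the two-sided chance of rejecting the null one is 2.5% as written. Under Holm it is 4.4% at correlation 0.3 and 3.9% at 0.8. In the favourable direction only, it goes from about 1.25% to about 2.5%.

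**The case against.** The strongest reply is that nothing here is wrong. An equal Bonferroni split is a standard, valid choice for an either-endpoint rule; level, success rule and sample size are consistent; and the trial is neither required nor sized to show both endpoints. That stands. A reader might infer from the gain in the table that the trial loses 7 to 10 points of power for its main conclusion. The article does not support this: success is declared on one significant endpoint, and power for at least one rejection is identical under both methods.

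A reader might also infer that the stricter second test buys nothing. That goes too far. Holm keeps the 5% ceiling but uses more of it, and a false claim on a truly null second endpoint becomes more likely. In an open-label trial with self-reported scores, a sponsor could reasonably prefer the stricter level.

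Two further points stand in part. The calculation ignores the phase III interim, and a step-down must be combined with its boundaries, so the change needs a little more than one sentence. A fuller analysis plan, not shown, could also add a step-down, since Holm's first step is itself 2.5%. But the article does state 2.5% for both scores, so the point concerns a stated choice and not missing detail.

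**Conclusion.** The point holds as a minor suggestion. The fixed 2.5% per endpoint is valid, and neither the error control nor the power for the declared success rule is at fault. What can be improved is the chance of confirming both dimensions: 68–74% as written against 78–81% with Holm, or 81% against about 85–86% for a given endpoint. These figures assume that both planned effects are fully true, that 296 patients are evaluable, that there is no interim look, and that the correlation lies between 0.3 and 0.8. The correlation is an assumption throughout. The improvement costs no patients, and the added risk on a null second endpoint (2.5% to about 4% two-sided) stays within the 5% family-wise limit.

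**What to change.** Before any comparative outcome data are seen, replace the fixed level in the Statistical analysis section with Holm's procedure, and write out the 5% family-wise level:

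- Compare the smaller of the two p-values with 2.5% (two-sided). If it is significant, test the other endpoint at 5% (two-sided).
- Claim benefit only for the dimension or dimensions rejected, and keep the condition that the other score must not deteriorate as part of the overall superiority rule.
- If the phase III interim is kept, give each endpoint the spending boundary for 2.5%, and move the remaining endpoint to the boundary for 5% once the first has been rejected.

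Sample size, visits and data collection do not change. The cost is a short amendment, one extra rule for the interim boundaries, and the higher false-claim risk on a null second endpoint. If the sponsor prefers the stricter level for the second claim, keeping 2.5% for both is defensible and could be stated as a deliberate choice.

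### Screening factors at univariate p < 0.1 and then testing the survivors on the same data robs the p-values and intervals in the secondary change-score models of their nominal meaning

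*Protocol article*

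**What the plan says.** The Statistical analysis section of the Protocol article takes the phase III scores in three steps.

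- **Co-primary comparison, with the level set at 2.5%:** "a t-test will be done to compare FACT-F and physical well-being scores at 3 months according to the study arms, at the statistical level of" (the figure just given).
- **Second analysis of the same scores:** "An analysis of variance for repeated measure will also be done taking into account the baseline score".
- **Factor models:** "some univariate and multivariate models will be done in order to identify factors associated with the change of fatigue and physical well-being score", the change being that from baseline to month 3. The entry rule is "All factors with an univariate *p*-value < 0.1 will be eligible for the multivariate models".

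The phase III analysis population is "ITT patients with FACT-F and physical well-being score available at baseline and M3".

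The Randomization section names variables that are natural candidates for such models: "Randomization will be stratified per site, baseline level of fatigue, targeted therapy, number of lines of prior therapy in the metastatic status, and age".

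The article does not list the candidate factors, does not say whether the arm is one of them, and does not say how p-values or intervals from these models will be read. Those details may sit in the full protocol or analysis plan and are not criticised here. The p < 0.1 rule is stated, and so is the choice of change from baseline as the outcome.

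**The concern.** A p-value or 95% interval from a multivariable model has its usual meaning when the factor was put in the model without looking at its relation to the outcome. Here a factor is tested only after the same data have shown p < 0.1, that is, an absolute t above about 1.65. The right reference distribution is the one conditional on having passed, and an ordinary regression table does not use it.

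The purpose of these models is inferential: they are run "in order to identify factors associated with the change of fatigue and physical well-being score between baseline and 3 months". At stake is the published list of associated factors. Some entries will look well supported only because they were selected, and small real effects will look larger than they are.

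Two further consequences depend on what is offered to the screen. If the arm is a candidate, it can be dropped. If baseline FACT-F, or a category built from it, is a candidate for raw change in FACT-F, regression to the mean alone will make it appear associated.

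**Working it through.** **Number of patients.** The Sample size section states "with a bilateral alpha risk of 2.5%, a statistical power of 80%, and a 5% lost to follow-up rate, 312 patients will need to be" randomised, for 5 points with SD 13 and 2.5 points with SD 6.5. Both are 0.385 SD, and allocation is 2:1.

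- Control arm: (1 + 1/2) × (13/5)² × (2.241 + 0.842)² = 1.5 × 6.76 × 9.505 ≈ 96.4, so 97, and 291 in total.
- With 5% lost: 291/0.95 = 306.3, so 307. Rounding up to a multiple of 12 (four cohorts, 2:1) gives 312.

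The plan's figure is reproduced and not in dispute. Evaluable patients: 312 × 0.95 ≈ 296.

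**Null factor, by arithmetic.** If the final model barely changes the factor's p-value (independent candidates), P(p < 0.05 given p < 0.1) = 0.05/0.10 = 50%. For a null factor, interval coverage is one minus that rate, so also about 50%.

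**Null factor, by simulation.** Settings: n = 296, 2:1, screen at p < 0.1, survivors refitted together by least squares, nominal 5% tests. The number and correlation of candidates, and the 5% level, are assumptions. The first five rows use 4,000 runs each. The last two come from a separate simulation of 1,500 runs each, with baseline and month-3 scores correlated 0.5.

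| Null candidates | Mutual correlation | p < 0.05 given passed | 95% coverage given passed | Error per candidate, all counted |
|---|---|---|---|---|
| 5 | 0 | 52% | 48% | 5.3% |
| 10 | 0 | 49% | 51% | 4.9% |
| 15 | 0 | 49% | 51% | 5.0% |
| 20 | 0 | 50% | 50% | 5.0% |
| 10 | 0.3 | 26% | 74% | 2.5% |
| 15 | 0.2 | 33% | 67% | 3.2% |
| 20 | 0.2 | 32% | 69% | 3.1% |

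**Weak real factor.** With a true slope of 0.08 SD per SD, the factor passes in 40% of runs. Its mean estimate is then 0.136, about 1.7 times the truth. Its interval coverage is 93.5%, so here the harm is inflation rather than lost coverage.

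**The arm, only if it is screened.** With 198 and 99 patients, the standard error of the arm difference is √(1/198 + 1/99) = 0.123 SD. The chance of failing p < 0.1 is 90% with no effect, 79% at 0.1 SD, 51% at 0.2 SD and 7% at the design effect of 0.385 SD. When kept at a true 0.2 SD, the estimate averages 0.296 SD. These are in SDs of the change, which equal SDs of the score when baseline and month 3 correlate at 0.5.

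**Baseline score against raw change, only if it is offered.** With equal variances and baseline-to-month-3 correlation r (assumed), corr(change, baseline) = −√((1 − r)/2).

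- r = 0.5: correlation −0.50, |t| = 0.50 × √(294/0.75) ≈ 9.9.
- r = 0.7: correlation −0.39, |t| ≈ 7.2.
- A median split multiplies these correlations by about 0.8, leaving |t| near 7.5 and 5.6.

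In simulation a median-split baseline level was significant for change in every run. The same variable in a model of the month-3 score with the continuous baseline score included was significant in 4.7% to 6.3% of runs.

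**After the change.** With 10 null factors in a fixed list, the arm always in and a true arm effect of 0.2 SD, coverage is 95.0% for the null factors and 94.5% for the arm, and the mean arm estimate is 0.198 SD. The chance of at least one false factor is 39% (1 − 0.95¹⁰ = 40%), the same as with screening.

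**The case against.** The strongest reply is that this is a follow-on analysis with no alpha, decision or claim attached, and that the Aim and research questions section does not list factor-finding in these terms. Screening does not raise the false-positive rate per candidate: the table shows 2.5% to 5.3%. The conditional figures move with the assumed number and correlation of candidates. The candidate list, forced terms and reporting style are commonly left to a fuller document. All of this stands, and it limits the point to what is reported for selected factors in secondary models. It does not defend the stated rule, which suits the stated purpose poorly.

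A reader might infer three stronger things that the article does not support.

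- **That the arm will be screened out.** The text never says the arm is a candidate. The figure of about one half also needs a true effect near half the planned one; at the planned effect it is 7%.
- **That baseline fatigue is bound to appear as a predictor.** The article does not say which measure defines the fatigue stratum, and fatigue is measured by both FACT-F and a visual analogue scale. Nor does it say the stratum enters these models. If it is built from FACT-F, the artefact concerns change in FACT-F and does not carry over automatically to physical well-being.
- **That the efficacy result is compromised.** Neither the t-test nor the repeated-measures analysis passes through the screen.

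**Conclusion.** The point holds, within narrow limits. The p < 0.1 rule is the only selection rule stated, and it leaves p-values and 95% intervals of retained factors without their nominal meaning: about 26% to 52% of selected null factors are significant at 5%, with coverage of about 48% to 74%, and weak real effects are overestimated. These ranges assume 5 to 20 candidates, mutual correlation of 0 to 0.3, 296 evaluable patients and reporting at a nominal 5% without allowance for selection. The concerns about the arm and about baseline fatigue are conditional on what is offered to the screen. This is a cheap improvement to a secondary analysis. It does not touch the sample size or the confirmatory comparison.

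**What to change.** Replace the univariate screen with one prespecified model per scale, along these lines: the month-3 score is modelled on the continuous baseline score and the study arm, both always included, plus a short list of baseline factors fixed before the data are seen. The stratification factors are a natural start. Site would enter as a random effect or in groups, because 18 centres are planned. Targeted therapy would enter in a few classes, because the article names seven inhibitor classes. With the continuous baseline score in the model, a fatigue stratum built from it should not be reported as a factor associated with raw change.

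Report every term whatever its p-value, and label the analysis exploratory, because a fixed list restores interval coverage but does not remove multiplicity. If data-driven selection is still wanted, use a penalised model with arm and baseline score unpenalised, and bootstrap intervals that repeat the selection step.

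Cost: a few lines of text, and no new data or patients. The model carries more terms, so intervals for single factors will be somewhat wider (the amount was not calculated), and the list has to be agreed in advance.
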